# Assessing a Sleep Interviewing Chatbot to Improve Subjective and Objective Sleep: Protocol for an Observational Feasibility Study

**DOI:** 10.2196/45752

**Published:** 2023-05-11

**Keywords:** automated chatbot, behavior analysis, conversational agents, older adults, sleep disorders, sleep interview

## Abstract

**Background:**

Sleep disorders are common among the aging population and people with neurodegenerative diseases. Sleep disorders have a strong bidirectional relationship with neurodegenerative diseases, where they accelerate and worsen one another. Although one-to-one individual cognitive behavioral interventions (conducted in-person or on the internet) have shown promise for significant improvements in sleep efficiency among adults, many may experience difficulties accessing interventions with sleep specialists, psychiatrists, or psychologists. Therefore, delivering sleep intervention through an automated chatbot platform may be an effective strategy to increase the accessibility and reach of sleep disorder intervention among the aging population and people with neurodegenerative diseases.

**Objective:**

This work aims to (1) determine the feasibility and usability of an automated chatbot (named MotivSleep) that conducts sleep interviews to encourage the aging population to report behaviors that may affect their sleep, followed by providing personalized recommendations for better sleep based on participants’ self-reported behaviors; (2) assess the self-reported sleep assessment changes before, during, and after using our automated sleep disturbance intervention chatbot; (3) assess the changes in objective sleep assessment recorded by a sleep tracking device before, during, and after using the automated chatbot MotivSleep.

**Methods:**

We will recruit 30 older adult participants from West London for this pilot study. Each participant will have a sleep analyzer installed under their mattress. This contactless sleep monitoring device passively records movements, heart rate, and breathing rate while participants are in bed. In addition, each participant will use our proposed chatbot MotivSleep, accessible on WhatsApp, to describe their sleep and behaviors related to their sleep and receive personalized recommendations for better sleep tailored to their specific reasons for disrupted sleep. We will analyze questionnaire responses before and after the study to assess their perception of our proposed chatbot; questionnaire responses before, during, and after the study to assess their subjective sleep quality changes; and sleep parameters recorded by the sleep analyzer throughout the study to assess their objective sleep quality changes.

**Results:**

Recruitment will begin in May 2023 through UK Dementia Research Institute Care Research and Technology Centre organized community outreach. Data collection will run from May 2023 until December 2023. We hypothesize that participants will perceive our proposed chatbot as intelligent and trustworthy; we also hypothesize that our proposed chatbot can help improve participants’ subjective and objective sleep assessment throughout the study.

**Conclusions:**

The MotivSleep automated chatbot has the potential to provide additional care to older adults who wish to improve their sleep in more accessible and less costly ways than conventional face-to-face therapy.

**International Registered Report Identifier (IRRID):**

PRR1-10.2196/45752

## Introduction

### Overview

Evidence exists for a bidirectional relationship between sleep disorders in the aging population and people with neurodegenerative disease [1-3]. Specifically, between 40% and 70% of the older population report difficulties in sleep onset or maintenance and insomnia symptoms [4-6], which increase their risk of developing neurodegenerative disorders. Similarly, there is a high prevalence of sleep disorders, such as sleep apnea and circadian rhythm disorders, among people with neurodegenerative disorders [7-10], where sleep disorders can accelerate cognitive decline [11,12]. Moreover, neurodegenerative disorders affect not only patients but their entire households, especially the primary carer. Indeed, studies [13-16] have shown that approximately two-thirds of older adult caregivers have some form of sleep disturbance. Thus, early intervention of sleep disorders among older adults can improve their quality of life, reduce their risk of developing neurodegenerative disorders, and prevent further complications among household members.

Researchers have conducted clinical trials using cognitive behavioral therapy [17-19] and motivational interviews [20-22] to improve sleep quality among older people, people with neurodegenerative disorders, and their carers. However, one-to-one individual therapies (in-person or remote) and face-to-face group therapies may be costly and difficult to access.

Several digital insomnia tracking and treatment systems [23,24] have been developed and evaluated. For example, Zaslavsky et al [22] developed a mobile health (mHealth) monitoring and self-management app. mHealth monitors sleep quality through the wearable Fitbit Charge 2 and automatically sends text messages that provide weekly information and motivational feedback. Zaslavsky et al [22] showed that their proposed mobile app mHealth, combined with motivational interviews conducted by telephone, can significantly improve participants’ self-reported sleep quality after 19 weeks of participation. In addition, Aji et al [23] showed that a self-reporting mobile app (SleepFix), connected to a wearable sleep-tracking device, can encourage users’ engagement with the app’s self-reporting functionality in a pilot randomized controlled trial.

However, these studies only combine digital sleep quality monitoring with a digital self-reporting mechanism or periodic text messages to encourage users to engage in sleep quality reporting, good sleep habits, and routine. They do not engage in conversations that may further encourage information sharing and behavioral changes. To engage more actively with users, Rick et al [24] proposed a Telegram-based chatbot, SleepBot, that dynamically enquires about users’ sleep information based on preprogrammed questions. Aarts et al [25] proposed a chatbot Snoozy for children aged 8-12 years with sleep difficulties, which asks children how their sleep was, the reasons for it if they slept poorly, and what behavioral methods they have tried to help with their sleep. Aarts et al [25] showed that a chatbot could help collect subjective reports from children over sustained period instead of traditional diaries.

In this feasibility study, we propose a sleep intervention chatbot design named MotivSleep. Our proposed MotivSleep first triages participants’ sleep based on information gathered from a contactless sleep-tracking analyzer. Then, MotivSleep starts conducting sleep interviews only when the sleep analyzer identifies a bad night’s sleep. The automatic sleep interview asks participants about any potential adverse factors that might have affected their sleep the night before, prior to using this information to provide personalized recommendations for better sleep (ie, healthy habits that you can practice during the day to help you get a good night’s sleep) [26] and encouraging them to maintain good sleep habits.

### Design Engineering Process

This work is built upon automated and manual monitoring and care procedures followed by the Care Research and Technology Center (CRT), part of the UK Dementia Research Institute (UK DRI). The design of our proposed MotivSleep chatbot involved an advisory group with patients and health care professionals from its conception, following the identified key characteristics in developing human-centered care technologies [27]. Specifically, carers, health professionals, occupational therapists, sleep specialists, chatbot researchers, and designers have come together in 2 workshops where the needs and values of the stakeholders were discussed [28]. We also requested input from the advisory board, conducted interviews with people living with dementia and their carers, conducted patient and public involvement and engagement sessions with healthy older adults, and surveyed results to develop initial dialogue plans that can conduct sleep interviews through chatbot.

Based on information and advice from the groups mentioned above, we built a sleep management chatbot integrated with WhatsApp. This internationally available messaging platform provides instant text and voice messaging services through the American company Meta Platforms. To access the proposed MotivSleep chatbot, we will gather the participants’ phone numbers and add them to the MotivSleep database, where messages will be sent out automatically at the user’s preferred time, potentially daily. Additionally, we will use the Withings sleep analyzer, a commercially available contactless device, to monitor and track participants’ objective sleep parameters. The sleep analyzer can be installed under the participant’s mattress, and the information gathered can be accessed through an API. The Withings sleep analyzer is chosen due to its passive recording ability (ie, it does not need recharging or adjustments once installed) and previous collaboration between UK DRI and Withings that provides easy integration. Additionally, the Withings sleep analyzer has been evaluated and showed comparable results to actigraphy and polysomnography based sleep assessment, in older people [29]. In this study, we will analyze participants’ sleep data to monitor the participants’ objective sleep parameters based on respiration, heart rate, snoring, and apnea episodes. This analysis triggers the conversation stage of our proposed MotivSleep chatbot.

The chatbot component of our proposed MotivSleep chatbot will automatically start a conversation with the user at least twice a week, on Wednesdays and Saturdays, to prevent data scarcity and ensure we collect data from all participants. In addition to the previously mentioned 2 days, the chatbot will start the conversation when the server detects anomalous sleep patterns from the participant’s data. Other than on these occasions, MotivSleep will not start the conversation to avoid too many repetitive requests for information from participants. Furthermore, participants can trigger the chatbot at any time by initiating the chat (ie, by sending “Hi MotivSleep” to the chatbot). The architecture of MotivSleep is shown in Figure 1 and is based on the Distinguish Business Logic from ML Model pattern [30].

**Figure 1 figure1:**
[figure not shown]
The architecture of the proposed MotivSleep chatbot. UI: user interface.

Specifically, MotivSleep consists of 3 layers: a presentation layer, a logic layer, and a data layer, as follows:

The presentation layer provides a user interface to conduct interviews where participants interact with MotivSleep delivered through WhatsApp. Backend structures allow MotivSleep to acquire sleep data from the Withings sleep analyzer.The logic layer that provides the chatbot logic to manage the chatbot dialogue based on predefined dialogue routes, a sleep assessments triage module that analyzes participants’ sleep assessments using pretrained machine learning models, and an interview route selector that selects conversation paths based on sentiment analysis and topic modeling using machine learning models.The data layer that provides data storage for participants’ conversation history and sleep data gathered from the Withings sleep analyzer.

### Chatbot Features

The participants will interact with the WhatsApp chatbot and have a Withings sleep analyzer installed to track their sleep. Our system’s backend server is connected to the Withings sleep analyzer database. The sleep monitoring data is accessible through the designed triage mode and the chatbot feature, with which the participants can interact. Specifically, MotivSleep accesses participants’ sleep-tracking data in the morning and triages their objective parameters. The triage will result in three signals, as follows:

Red: an anomalous night with significant differences from the usual (ie, gathered 2 weeks before the start of the chatbot engagement) patterns is detected. Specifically, this relates to participants’ bedtime, wake-up time, the number of times they leave the bed during the night, and the duration of snoring time.Yellow: when the model detects ongoing problems in their sleep.Green: when there are no significant differences in sleep patterns or other existing sleep problems.

The MotivSleep chatbot follows a dialogue route with multiple branches, which may end or continue the conversation. Figure 2 shows the dialogue design of our chatbot. Specifically, our chatbot is designed with seven stages, as follows:

The objective sleep assessment: sleep quality is highly challenging to assess, with a range of potential models for data fusion from the internet of things devices. In the context of our study, we will initiate analyses of the objective sleep assessment using measures provided by the installed Withings sleep analyzer. Specifically, MotivSleep starts at a predefined time each day and calculates the sleep quality using the sleep tracking device. If the triage result is red or yellow, MotivSleep will continue to the next stage to start the chatbot and engage with the participant; otherwise, MotivSleep will not send the initial text message and will quit automatically. We note that the UK DRI CRT has ongoing work in sleep quality evaluation using the Withings sleep analyzer, which could be incorporated into the study for comparison when available.The subjective sleep assessment: MotivSleep chatbot activates the interview through WhatsApp and asks the participant, “Did you sleep well last night?” This stage helps MotivSleep confirm with the participant if they had a bad night’s sleep. If the participant denies having had a bad sleep, our chatbot will go to stage 7, wishing them a good day and quitting. However, if the participant confirms that they have had a bad night, the chatbot will continue to ask the next question.Redocumentation of consent: the chatbot will briefly remind the participant about the study, ask them for their consent to participate in the current interactions, and provide insights into their poor sleep. If they do not consent, the chatbot will go to stage 7, where we thank them for their engagement, and the chat ends; otherwise, the chatbot will continue to the next stage.The information-seeking stage: in this stage, the chatbot will ask the participant for reasons that might explain why they did not sleep well the previous night. This open question seeks insights into participant’s behaviors before and during their sleep that may have contributed to a bad night’s sleep. Answers to this question are collected and analyzed, and the analysis result will prompt the following three types of further questions:In-depth questions related to predefined specific reasons that cause their poor sleep. These questions will be triggered if we identify predefined reasons from the participant’s answers;Multiple-choice questions consist of potential reasons that might cause poor sleep. These questions will be asked if the participant answers that they do not know why they had a poor sleep;Similar questions to the previously asked question (ie, why did you sleep poorly?) until they confirm there is no more information to add. These questions will be asked if the reasons the participant provided early are not one of the predefined reasons.Agreement to receive personalized recommendations for better sleep: in this stage, the chatbot will ask the participant whether they want to hear personalized recommendations for better sleep. If they disagree, the chatbot will go to stage 7, where we thank them for their engagement, and the chat ends; otherwise, the chatbot will continue to the next stage.Provide personalized recommendations for better sleep: in this stage, we provide specific recommendations to the participant based on the information gathered during stage 4. Furthermore, we provide a motivational summary of what was covered today, including their reasons for poor sleep and recommendations for better sleep.The end of the conversation: in this stage, we thank the participant for the engagement, wish them a good day, and end the conversation. To further motivate the participants, the chatbot also praises the participant if some of the repeated behaviors negatively affecting their sleep were not mentioned in this interaction.

**Figure 2 figure2:**
[figure not shown]
Chatbot dialogue design. Note that the black ovals denote the start and the end of the skill, the yellow rectangles denote the dialogue by the chatbot, and the blue rectangles and the blue diamond denote the participants' inputs. The orange diamonds denote the diverging options.

This chatbot aims to perform knowledge transfer, that is, using the information gathered from the fourth stage to provide personalized recommendations for better sleep in the sixth stage, thus transferring knowledge on better sleep to the participants.

### Research Questions

The MotivSleep chatbot used in this feasibility study has been co-designed with patients, carers, and other health professionals. Together, we identified the following research questions:

*RQ1* Is our proposed MotivSleep chatbot accessible to participants, and how feasible is it to engage the participants with interviews using MotivSleep? We focus on assessing the feasibility and usability of our proposed MotivSleep, by measuring the number of turns and time spent chatting with the skill per engagement. Moreover, we assess MotivSleep’s accessibility by asking participants to rate their willingness to promote the chatbot using the net promoter score (NPS) [31] question in the exit questionnaire. Finally, we assess the participants’ perception of the chatbot by asking participants to complete the Godspeed Perceived Intelligence subscale (GPIS) [32] and Trust Perception Scale-Human Robot Interactions (TPS) [33] questionnaires.*RQ2* Can our proposed MotivSleep chatbot help improve participants’ subjective sleep assessment? We aim to evaluate the participants’ self-reported sleep assessment to analyze if the proposed MotivSleep helps participants to subjectively sleep better through the completion of the Epworth sleepiness scale (ESS) [34], Insomnia Severity Index (ISI) [35], modified Pittsburgh sleep quality index (PSQI) [36], and the single-item sleep quality scale (SQS) [37], conducted at the beginning, the end, and every 2 weeks throughout the study.*RQ3* Can our proposed MotivSleep chatbot help improve participants’ sleep, measured using the Withings sleep analyzer? We aim to analyze participants’ objective sleep assessments using sleep recordings gathered by Withing sleep analyzer throughout the study.

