## Methods

### Overview

Once reviewed by the Imperial College Research Ethics Committee, we will recruit 30 healthy older adults (aged 65-90 years) in 3 cohorts through the UK DRI CRT community outreach group community outreach in West London. Participants will have access to the conversational agent through WhatsApp chat. We estimate that the average conversation will take less than 10 minutes. Each participant will also have access to the Withings sleep analyzer provided by the research group.

A poststudy questionnaire consisting of the GPIS, TPS, and NPS will be completed when the participant finishes the study. We analyze participants’ answers to assess the participants’ opinions on the proposed MotivSleep chatbot’s intelligence, trustfulness, and participants’ satisfaction with MotivSleep, to answer RQ1. Additionally, all participants will complete the ESS, ISI, modified PSQI, and SQS questionnaires before the start, fortnightly during the study, and at the end of the study. We analyze the answers to these questions to investigate RQ2.

The first cohort of 10 participants will use both the Withings sleep analyzer for 6 weeks (the first 2 weeks aims to establish baseline sleep assessments without the usage of MotivSleep) and the WhatsApp chatbot for 4 weeks, with WhatsApp message reminders to encourage WhatsApp chatbot engagement sent out fortnightly (ie, twice for the first cohort of 10 participants). The first batch of participants’ feedback and engagement measures will inform a new iteration of improvements.

The second cohort of 10 participants and the third cohort of 10 participants will use the WhatsApp chatbot for 8 weeks and 12 weeks and the Withings sleep analyzer for 10 weeks and 14 weeks, respectively. Participants will be reminded fortnightly (ie, 4 times for the second cohort participants and 6 times for the third cohort participants) to encourage participation with the WhatsApp chatbot when activated. After each cohort, participants’ technical feedback will be addressed by improving the software.

The feasibility study will have a single experiment condition that includes three types of features:

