A sleep tracking device (ie, Withings sleep analyzer) and sleep analysis model.A chatbot (ie, MotivSleep) hosted on WhatsApp that conducts sleep interviews. The dialogue is designed to understand the reason behind participants’ sleep problems, provide personalized recommendations for better sleep, and support behavior changes to improve their sleep assessments.WhatsApp messages that encourage interaction with MotivSleep.

We will measure three classes of outcome variables as follows:

Assess the feasibility and usability of our proposed chatbot MotivSleep (RQ1)—the number of interactions in each MotivSleep conversation and time spent chatting with MotivSleep, and the poststudy questionnaire consisting of NPS, GPIS, and TPS.Assess the subjectively perceived sleep assessments (before, during, and after the study) (RQ2)—ESS, ISI, PSQI, and SQS questionnaires.Assess the objectively measured sleep assessments (before, during, and after the study) (RQ3)—obtained from the Withings sleep analyzer and analyze using the Withings provided sleep analysis models.

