### Limitations

Our study requires participants to use 2 devices (a Withings sleep analyzer and a smartphone to access WhatsApp) and complete web-based questionnaires. As such, older people unfamiliar with or unwilling to use these devices might self-exclude. However, successful findings from this study could be leveraged to revise further to allow for more accessible options on the technological design for a broader audience and users. Additionally, excluding participants with diagnosed life-threatening illnesses and severe mental health problems is a limitation. However, for this preliminary study, such exclusion is warranted to ensure that participants are medically stable and not reporting severe clinical symptoms that would require a higher level of care, which a digital chatbot cannot help treat.

Furthermore, we acknowledge the small number of participants in this feasibility study. Thus, we do not expect to find significant differences with respect to gender or age. However, the proposed sample size aligns with previous research on the number of participants needed to assess usability and feasibility.

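### The RQ1 usage measures describe conversations that took place, so they need not fall when prompts go unanswered, and the recommendation score is labelled as accessibility

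*Protocol article*

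**What the plan says.** Under Research Questions, RQ1 asks whether the chatbot is accessible and how feasible it is to engage participants in interviews. Feasibility and usability are assessed "by measuring the number of turns and time spent chatting with the skill per engagement". The outcome list in Methods, Overview gives "the number of interactions in each MotivSleep conversation and time spent chatting with MotivSleep", plus the exit questionnaire.

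For accessibility, RQ1 states: "we assess MotivSleep’s accessibility by asking participants to rate their willingness to promote the chatbot". On timing, Methods, Overview states: "A poststudy questionnaire consisting of the GPIS, TPS, and NPS will be completed when the participant finishes the study". The same paragraph reads that questionnaire as showing opinions on intelligence, trust and satisfaction.

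Chatbot Features describes what sets the length of a chat. At stage 2, "If the participant denies having had a bad sleep, our chatbot will go to stage 7, wishing them a good day and quitting". Refusing consent (stage 3) or refusing recommendations (stage 5) also leads to stage 7. At stage 4, a reason outside the predefined list brings further similar questions "until they confirm there is no more information to add".

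**The concern.** RQ1 is about whether people engage. A mean over engagements takes the engagement as given. If a growing share of prompts is ignored while the answered chats keep their length, the mean stays where it was.

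Length itself is ambiguous. Few turns can mean a good night, a refusal or difficulty with the system. Many turns can mean a willing participant or a chatbot that did not recognise the reason given. If sleep improves as the study hypothesises, chats would tend to shorten, and a reader could take that as falling engagement.

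NPS asks whether a user would recommend the chatbot, which is different from whether that person could reach and operate it. Participants who stop before the exit questionnaire do not contribute to it.

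The Conclusions say that evidence of feasibility will support a larger trial, and the Discussion stresses use over a prolonged period. Waning response is the obvious threat to both, and the listed usage measures can miss it.

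**Working it through.** The article gives no target, threshold or precision for these measures, so there is no stated figure to reproduce beyond the design counts. Those agree: 3 × 10 = 30 participants; fortnightly reminders over 4, 8 and 12 weeks = 2, 4 and 6.

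**1. Denominators.** The listed RQ1 outcomes are turns or interactions (per engagement or per conversation), time chatting, NPS, and the intelligence and trust scales. None is divided by prompts sent or by people enrolled. The Analysis Plan uses the transcripts for time spent and reported behaviours, not for non-response.

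**2. Turns and minutes against response.** Design Engineering Process has the chatbot start a conversation at least twice a week. Minimum prompts per person are then 2 × 4 = 8, 2 × 8 = 16 and 2 × 12 = 24. Over 10 people per cohort that is 80 + 160 + 240 = 480. Assume 8 turns and 5 minutes per answered chat.

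| Prompts answered | Turns per engagement | Minutes per engagement | Turns per prompt sent | Minutes per prompt sent |
|---|---|---|---|---|
| 480 (100%) | 8.0 | 5.0 | 8.0 | 5.0 |
| 360 (75%) | 8.0 | 5.0 | 6.0 | 3.75 |
| 240 (50%) | 8.0 | 5.0 | 4.0 | 2.5 |
| 120 (25%) | 8.0 | 5.0 | 2.0 | 1.25 |
| 48 (10%) | 8.0 | 5.0 | 0.8 | 0.5 |

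The same holds for two people with 24 prompts each and 6 turns per chat. One answers 24 (24 × 6 / 24 = 6) and the other answers 2 (2 × 6 / 2 = 6). Response is 24/24 = 100% against 2/24 = 8.3%.

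**3. NPS against loss before exit.** Assume 60% promoters and 20% detractors among completers, so NPS = 60 − 20 = +40 whatever the number lost. As a pessimistic bound, count the d people lost as detractors: NPS = 100 × [0.4 × (30 − d) − d] / 30. For d = 0, 3, 6, 9 and 12 this gives +40, +26, +12, −2 and −16.

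**4. The denominator that a response share would need.** The sections disagree on when a prompt is sent. Introduction, Overview starts interviews only after a bad night. Design Engineering Process adds two fixed days each week regardless. Chatbot Features sends nothing after a green triage. For a third-cohort participant the minimum is 24 prompts under the fixed-day rule and 0 under the triage-only rule, where the share could be undefined.

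**5. Precision of a mean per-person response share.** Half-width = t × SD / √n. The cohorts differ in duration, and the software is revised between them, so n = 10 is the relevant size: 2.262 / √10 = 0.715. This gives 0.715 × 0.3 = 0.21 at an assumed SD of 0.3, and 0.715 × 0.5 = 0.36 at SD 0.5. Pooling all 30 would give 0.373 × 0.3 = 0.11, but that averages over three different exposures.

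**The case against.** Several points on the other side are fair.

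- *The term engagement is not defined.* An unanswered prompt could be counted as a conversation with no participant turns, and ignored prompts would then lower the mean. The article does not say this. It does leave room for it, so it would be too strong to infer that unanswered prompts certainly never enter.
- *Time has no per-engagement unit in the outcome list or the Analysis Plan.* Total time per participant would separate the two people in the example. RQ1 itself, however, fixes the unit as per engagement.
- *Other measures serve RQ1.* The intelligence and trust scales are listed, and engagement measures are mentioned after the first cohort. A reader might infer that RQ1 cannot be answered at all, but the documents do not support that. Still, the scales measure perception, and the engagement measures are undefined and serve software revision.
- *A condensed article may leave response and retention to a fuller document.* This is so for detail. The point here is limited to outcomes that the article fixes, and to a label that it attaches to NPS.
- *People who never enrol.* A reader might go further and fault the study for not counting those who cannot use the system. RQ1 asks about accessibility to participants, Recruitment admits only willing people with home internet, and Limitations concedes that "older people unfamiliar with or unwilling to use these devices might self-exclude". That limit is disclosed, so counting such people would be an optional addition.
- *Extreme non-response is hypothetical.* Fortnightly reminders and payment partly for engaging with the chatbot make it less likely. This stands: the example shows how the measure behaves and forecasts nothing.

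**Conclusion.** The concern holds in a limited form. As naturally read, the listed usage measures can stay constant while response falls from 100% to 10%, and chat length has no clear good direction because the dialogue branch determines it. NPS is mislabelled: the article calls it accessibility in one section and reads the questionnaire containing it partly as satisfaction in another.

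This rests on reading engagement and conversation as exchanges that took place. Turns, minutes, promoter shares and SDs are assumptions. The prompt counts hold only under the twice-weekly rule, which other sections contradict. The documents do not show that response will be poor, or that RQ1 is unanswerable once response is added.

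**What to change.** 1. Reconcile Introduction (Overview), Design Engineering Process and Chatbot Features on when the chatbot sends a prompt, so that the denominator is fixed. Define engagement at the same time.
2. Make the main engagement measure the share of chatbot-started prompts answered. Compute it per participant over all enrolled, with non-users counted as zero. Average over participants and show it by cohort and week of use, with the precision for each cohort. Report participant-started chats separately.
3. Report the share of prompts sent that reach stage 6, with exits for a good night, refusal and non-response shown separately. Restricting this to confirmed bad nights would again condition on having answered.
4. Keep turns and minutes as descriptors by dialogue branch.
5. Report NPS as satisfaction, with the number of enrolled participants who did not complete the exit questionnaire.

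The cost is small. Conversation history is already to be stored. Outgoing prompts must be logged as well, which the article does not state, and some analysis is added. Screening-log reasons and first chats completed unaided are optional; the latter would need new observation.
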